### Assessments

#### Assessment of eligibility for inclusion

Eligibility for inclusion of patients will be assessed by using the Clinician-Administered PTSD scale for DSM-5 (CAPS-5) [29, 30]. A symptom is considered present only if the corresponding severity score is rated 2 or higher (on a 0–4 scale) [29]. When a patient scores positive on all the symptoms belonging to PTSD, the diagnosis is established. As part of the CAPS-5, the Life Events Checklist for DSM-5 (LEC-5) [31], will be used to screen and identify repeated or multiple sexual and/or physical abuse before the age of 18 years by a carer or other person in a position of authority. In order to exclude patients with high risk of suicidality, those with a score of 3 on item 9 of the BDI-II [24, 32] will be excluded.

#### Main outcome variable

The main study parameter will be the severity of PTSD symptoms, assessed by the PTSD Symptoms Scale-Self Report [33, 34]. This is a 17-item self-report scale developed as a brief measure of PTSD symptom frequency in trauma victims. Items are scored on a 4-point scale from 0 (“not at all/only one time”) to 3 (“almost always/five or more times a week”). The English version [33] and Dutch version [35] have good psychometric properties.

The Brief Symptom Inventory [48, 49] will be used to measure symptoms of general psychopathology. This is a self-report instrument measuring the severity of complaints. Each item can be rated on a 5-point scale from 0 (not at all) to 4 (a lot). The reliability, validity, and utility of the BSI have been tested in more than 400 research studies [50, 51]**.**

The Structured Clinical Interview for DSM-IV Axis II personality disorders (SCID-II) [52] will be used to determine the presence of a personality disorder (cluster B and C). This interview is considered as the gold standard in semi-structured assessment instruments for personality disorders. The Dutch translation and adaptation was developed by Weertman, Arntz, and Kerkhofs [53] and validated by Weertman Arntz, Dreessen, Van Velzen, and Vertommen [54].

The EQ-5D will be used to index health-related quality of life [55]. This is a questionnaire consisting of five dimensions with three levels each (from having no problems until being unable to execute an activity). The questionnaire has been validated in different groups and in different countries [56].

Healthcare consumption and productivity loss in patients will be indexed to measure the cost-effectiveness of both treatments, using a case record form based on a form used in other studies [57–59].

Other variables that will be included in the study are age and gender of the participating patients, and socio-economic status, psychotropic medication use at baseline and during treatment, and level of education. After the first session in which psycho-education is given and a case-conceptualisation is made, the expectancy rating of the therapist and the patient will be measured by asking to what extent they expect that the patient will profit from the treatment to which he or she is allocated, using a VAS scale from 0 (not at all) to 100 (totally). Drop-out rate and deterioration of the patient will be registered (i.e., the number of extra face-to-face contacts with a healthcare professional, including additional medication consultations, to avoid crises). Patients who drop out of the study will engage in assessments at every time point as far as possible.

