**Discussion:**

The study results may help to inform the ongoing debate about whether a phase-based approach has added value over immediate trauma-focused therapy in patients suffering from PTSD due to childhood abuse. Furthermore, the results will contribute to knowledge about the safety, efficacy, and cost-effectiveness of treatments in this target group.

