It has been argued that individuals with a history of childhood abuse who suffer from symptoms of complex PTSD may be insufficiently stable to tolerate evidence-based immediate trauma-focused treatment [8, 12]. In 2011 the International Society for Traumatic Stress Studies (ISTSS) Complex Trauma Task Force published the results of a survey meant to obtain expert opinions about the treatment of patients with symptoms of complex PTSD [13] showing that 85% of the experts reported that they would use a phase-based approach as their first line of treatment. Based upon these results, a phase-based treatment has been recommended for these patients [8], in which trauma-focused treatment (phase II) is preceded by a stabilization phase (phase I) aimed at ensuring the individual’s safety, reducing self-regulatory problems, and improving emotional, social, and other psychological skills. This phase-based approach is then completed with a reintegration phase (phase III), aimed at consolidating treatment gains and helping the person to adapt to his or her present life circumstances [8]. In clinical practice, the phase I treatment for PTSD with symptoms of complex PTSD varies from eight weekly sessions (i.e., the programme Skills Training in Affective and Interpersonal Regulation (STAIR)) [14] up to programme with a much longer duration [15, 16]. In the guidelines of the ISTSS the majority of the experts considered 6 months as a reasonable length for phase I [8].

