
## Methods/design

### Aim

The purpose of the current study “ToPrepareOrNot” (TOPRON), is to determine whether a phase-based approach is more effective than immediate trauma-focused treatment in individuals with PTSD related to repeated childhood abuse, and possible symptoms of complex PTSD. For the trauma-focused condition we used eye movement desensitization and reprocessing (EMDR) therapy, because it is one of the guideline treatments for PTSD [2] with an efficacy similar to PE. Our first hypotheses is based upon the current guidelines for the treatment of complex PTSD [8], and expert consensus about the treatment of this target population [13]; that is, that the phase-based treatment condition (i.e., STAIR/EMDR) is significantly more effective in PTSD (severity of PTSD symptoms and proportion of diagnoses lost) than the immediate trauma-focused condition (i.e., EMDR/EMDR). Our second hypothesis is that the phase-based treatment approach leads to a significantly better outcome in terms of reduced symptoms of complex PTSD and comorbid symptoms, drop-out rate, quality of life, and health care consumption than the immediate trauma-focused condition. An additional aim is to investigate potential moderators and predictors of drop-out or treatment (non) response. To this end, we hypothesized that signs of affect dysregulation and having interpersonal problems at the start of therapy would be related to worse outcome in the trauma-focused condition [19, 20]. We also expect patients with a comorbid personality disorder [21] and high level of dissociation at the start of therapy [22] to be more at risk of deterioration and drop-out in both conditions.

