### Study design

The TOPRON study entails a randomized controlled trial with two arms: a phase-based treatment approach (STAIR-EMDR) versus a trauma-focused treatment condition (EMDR therapy only). In the STAIR-EMDR condition, patients will receive eight sessions of stabilization treatment (STAIR), followed by 16 sessions of EMDR therapy, adding up to a total number of 24 treatment sessions. In the trauma-focused condition, patients will receive 16 sessions of EMDR therapy. All sessions last 90 min. The two groups will be compared on a number of variables before treatment, after every eighth session, post-treatment and at follow up, that is 3 months and 6 months after the post-treatment session (see Figs. 1 and 2). By assessing every eight sessions it will be possible to determine the added value of a stabilization phase examining the results after an equal amount of sessions. For this study, we chose to use a fixed number of sessions. All patients in the STAIR-EMDR condition will receive eight sessions STAIR while in both conditions patients will receive a maximum of 16 sessions of EMDR. When all targets are processed to a Subjective Unit of Distress (SUD) score of 0 and a Validity of Cognition (VoC) score of 7, the patient will be assessed to determine whether he or she no longer meets the criteria for PTSD. In the case of early completion, the remaining sessions are cancelled. Because STAIR is meant as a first-phase treatment prior to the start of trauma-focused treatment (i.e., EMDR therapy) following STAIR, all patients will receive EMDR therapy. That is the reason that early completion during STAIR is not possible.

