### Procedures

During the regular intake procedure conducted by a clinician not involved in this study and without influence on assignment to the conditions, patients with PTSD due to repeated sexual and/or physical abuse during childhood will be asked to participate in the study. After their approval by signing an informed consent form, they will be assessed on the inclusion and exclusion criteria.

After assessment for eligibility (T0) and baseline assessment (T1; see Fig. 1), the patients will be randomly assigned to one of the two conditions. The randomization will be executed by a computerized randomization programme [28], creating a list of randomized assignment per location (strata). Randomization blocks of six or eight will be employed (divided over four strata based on treatment location) and generated by a study-independent collaborator. The assignments will be put into envelopes per location and will be picked for each patient in order from top to bottom as listed by the computerized randomization. Within each randomly assigned condition, the participants will be assigned to one of the therapists, based on availability. During treatment, assessments will take place after every eight sessions, post-treatment, and at 3 and 6 months follow up.

Due to the nature of the trial, participants and clinicians in the study cannot be blinded to treatment assignment. The research assistants (students studying for a Master’s degree in psychology) who will carry out the assessments will receive intensive training on the interviews and do not have any interest in the outcomes of this study.

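### Deterioration is defined only as a count of extra contacts, so the hypothesis about who deteriorates would test service use and not worsening

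*Protocol article*

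**What the plan says.** The protocol article states, under Secondary outcome variables: "Drop-out rate and deterioration of the patient will be registered". The bracket that follows opens with *i.e.* and reads "the number of extra face-to-face contacts with a healthcare professional, including additional medication consultations, to avoid crises". Only contacts appear in that bracket, so the count is the definition of deterioration and not one example of it.

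Deterioration is then the outcome of a stated hypothesis. Under Aim, patients with a comorbid personality disorder or high dissociation at the start are expected "to be more at risk of deterioration and drop-out in both conditions". The abstract's Discussion adds that "the results will contribute to knowledge about the safety, efficacy, and cost-effectiveness of treatments in this target group".

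On blinding, Procedures says that "participants and clinicians in the study cannot be blinded to treatment assignment".

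The trial already has a repeated symptom measure. Under Main outcome variable: "The main study parameter will be the severity of PTSD symptoms, assessed by the PTSD Symptoms Scale-Self Report". Study design places the assessments "before treatment, after every eighth session, post-treatment and at follow up". Data analysis compares the arms on continuous measures by linear mixed models. It states no criterion for an individual patient getting worse.

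**The concern.** An extra contact made to head off a crisis is a response to perceived risk. It is not the worsening itself, and three problems follow.

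- **Wrong construct.** A precautionary contact that succeeds counts as deterioration. A patient whose symptoms rise clearly but who neither asks for nor receives extra contact scores zero.
- **Open to expectation.** Whether a contact takes place may depend on knowledge of the arm or of the patient's risk profile. Background reports a survey in which "85% of the experts reported that they would use a phase-based approach as their first line of treatment", so the belief that these patients are fragile under immediate trauma work is widespread in the field.
- **Unequal time.** A raw count grows with time under observation, and the arms have treatment phases of different length.

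At stake is the hypothesis on personality disorder and dissociation. If such patients are watched more closely, the count could seem to confirm it without any excess worsening. The article would then report a finding about service use under the name of deterioration.

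**Working it through.** **Figures in the plan.** The article gives no figure for deterioration. Its sample size reproduces: for the group-by-time interaction with f = 0.10, correlation 0.5, 5 occasions and N = 122, the noncentrality is 0.10² × 122 × 5 / (1 − 0.5) = 12.2 on 4 and 480 degrees of freedom, and power is 0.805. That figure does not depend on how deterioration is defined.

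**Time at risk.** Study design gives 24 sessions against 16, and Interventions gives two sessions a week for both therapies. If all sessions are used:
- Treatment phase: 24/2 = 12 weeks against 16/2 = 8 weeks; 12/8 = 1.5.
- To the last follow-up, taking 6 months as 26 weeks: 38/34 = 1.12.

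Equal weekly contact rates would thus give a 1.5-fold count in STAIR-EMDR during treatment, or 1.12-fold to the last follow-up.

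**Effect of differing contact thresholds (assumed rates; the article gives none).** Take two groups with the same true risk of worsening. Let an extra contact follow worsening in 80% of cases in one group and 40% in the other, and count any contact as deterioration.

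| True risk in both | Recorded | Ratio | Significant with 61 per group |
|---|---|---|---|
| 10% | 8% v 4% | 2.0 | about 15% |
| 20% | 16% v 8% | 2.0 | about 27% |
| 30% | 24% v 12% | 2.0 | about 41% |

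With 80% against 50% the ratio is 1.6, and the last column becomes about 10%, 16% and 24%. The ratio holds for any two groups, such as patients with and without a personality disorder. The last column needs two groups of 61, which fits the arms (122/2). The split by personality disorder is unknown.

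**A symptom-based alternative from data already collected.** PSS-SR has 17 items scored 0 to 3, so it runs from 0 to 51. The reliable-change threshold is 1.96 × SD × √(2(1 − r)). SD and r are not in the article and are assumed:

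| | r = 0.90 | r = 0.80 |
|---|---|---|
| SD 8 | 7.0 | 9.9 |
| SD 10 | 8.8 | 12.4 |

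**Number of looks.** With all sessions used, STAIR-EMDR has five post-baseline assessments (after 8, 16 and 24 sessions, 3 months, 6 months). EMDR only has four (after 8 and 16 sessions, 3 months, 6 months). At 2.5% false worsening per look, treated as independent:
- five looks: 1 − 0.975⁵ = 11.9%
- four looks: 1 − 0.975⁴ = 9.6%
- ratio 1.23

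A rule of worsening at any scheduled assessment would therefore bring in an imbalance of its own. Using four assessments in both arms (after 8 sessions, post-treatment, 3 and 6 months) gives 9.6% in each.

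**The case against.** Several stronger readings are tempting, and the article does not support them.

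- **That unblinded trial clinicians arrange the contacts.** The article says only that they are with a healthcare professional. The patient may ask, and the professional may be outside the trial. What stands is that patients and trial clinicians know the arm, so the threshold for contact may depend on it.
- **That service use alone answers the safety question.** Drop-out is registered separately, and the symptom scales are compared by mixed models with time as a category, so average worsening by arm would show. A mean can still improve while a minority gets worse.
- **That the plan rests an arm comparison on this count.** The deterioration hypothesis concerns predictors in both conditions. Randomisation makes arm independent of baseline predictors, so caution that differs by arm does not carry straight over to it. Caution that differs by risk profile would, though the article does not say whether those offering contacts know that profile.
- **That patients who leave simply count as not deteriorated.** Drop-out has its own record, and those who leave are to be assessed as far as possible.

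Two design features also help: all therapists deliver both conditions, and the expectancy of therapist and patient is rated. They reduce or expose bias but do not turn a contact count into a measure of worsening.

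The symptom-based alternative has limits too. PSS-SR is self-report by patients who know their arm, and it would miss crises between assessments. This argues for keeping the contact count beside it.

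**Conclusion.** The point holds as one about a stated definition. As written, deterioration means extra contacts, and the hypothesis that uses it would test service use. This is not a detail left to an analysis plan, because the article fixes the rule.

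The size cannot be read from the documents. The 1.5 and 1.12 time ratios assume that all sessions are used at the stated frequency, and they matter only if raw counts are compared between arms. The twofold spurious ratio rests wholly on assumed contact rates. The 7 to 12 point threshold rests on assumed SD and reliability. The sample size and the primary analysis are unaffected. The change is worth making because the hypothesis cannot be answered as posed without it, and the data are already planned.

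**What to change.** Add a prespecified deterioration measure: a rise in PSS-SR from baseline beyond a stated reliable-change threshold. Fix the SD and reliability behind it in advance.

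- Assess it in all randomised patients at the same four assessments in each arm: after 8 sessions, post-treatment, 3 months and 6 months.
- State how EMDR-only patients who complete before the eighth session are counted, since they may lack that assessment.
- Use it as the outcome for the hypothesis on personality disorder and dissociation, and for a descriptive comparison of the arms.
- Keep extra contacts under their own name, as a measure of service use and crises, reported per week at risk.

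The cost is a few lines of text and no new data. The downsides are small: a threshold must be chosen beforehand, self-report by unblinded patients remains, and crises between assessments are captured only by the contact count.

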### Power and sample size calculation

To our knowledge, methods for power calculation in the context of linear mixed models are unavailable. A power calculation based on repeated measures analysis of variance (ANOVA) was therefore used as a conservative approximation, with treatment condition as the between-subjects factor and time as the within-subjects factor. For 2 × 5 (between-subjects (treatment condition) × within (pre-treatment, after every eight sessions, post-treatment, 3 month follow up and 6 month follow up) repeated measures ANOVA (alpha 0.05, power 0.80, correlation between measures 0.5, and small effect-size (*f)* 0.10), a total sample size of 122 subjects will be required (*G* power) [60].

### Data analysis

Descriptive analyses will be used to evaluate demographic, clinical and baseline characteristics of both treatment arms. Analyses will be performed on the intent-to-treat basis and the sample of completers: the data of all randomized participants will be analysed using both groups as defined at randomization. On the continuous outcome measures, the groups will be compared using linear mixed models. Baseline scores will be included as covariates, time as a categorical variable, and treatment condition as a fixed effect.

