Until now, the safety and efficacy of the phase-based treatment approach for treating complex PTSD has been addressed in two studies [12, 14]. The first study used a randomized controlled trial (RCT) to compare the efficacy of STAIR (a phase I treatment) followed by prolonged exposure versus a waiting-list condition in a sample of female patients that suffer from PTSD as a result of childhood physical and/or sexual abuse [14]. The STAIR/exposure condition resulted in significant symptom reductions (i.e., PTSD severity, depression, general anxiety, dissociation), plus significant improvements in mood and anger regulation skills. In the STAIR phase, depression, anxiety, anger expression, and negative mood regulation improved significantly. There were no improvements in PTSD symptoms, dissociation, and alexithymia. The prolonged Exposure (PE) phase showed reductions in PTSD symptoms, dissociation, and alexithymia, and further improvements in depression and anxiety. No improvements were found in negative mood regulation and in anger expression in the PE phase. The results of this study suggest that the combination of STAIR/exposure is feasible and leads to a decrease in PTSD and a broad range of other symptoms associated with complex PTSD. One limitation of this study, however, was the relatively high drop-out rate in the STAIR/exposure condition (29% compared to 11% in the waiting list control group). Also, effect sizes pointed to the phase of exposure treatment conferring the bulk of the therapeutic benefits. Hence, although this study supports the effectiveness of a STAIR/exposure combination, the results do not provide univocal support for the contention that a phase-based treatment is superior to immediate trauma-focused treatment for individuals suffering from severe PTSD and symptoms of complex PTSD (see also [17]). Clearly, there was a need for direct comparison between a phase-based and an immediate trauma-focused treatment condition. Accordingly, in a second study, Cloitre and colleagues evaluated the efficacy of a phase-based treatment (STAIR/exposure) versus supportive counselling followed by prolonged exposure (support/ exposure) and versus STAIR followed by supportive counselling (STAIR/support) [12]. Women with PTSD related to childhood sexual and/or physical abuse were assigned to one of the three treatment conditions. The application of STAIR/exposure was found to be associated with greater benefits compared to the support/exposure condition in terms of self-reported reduction in PTSD symptom severity, interpersonal problems, and emotion regulation, but only at follow up (both 3 and 6 months). Immediately after treatment, all three experimental treatment conditions resulted in a substantial proportion of patients being PTSD negative (i.e., no significant differences were found between the three conditions). However, the lack of a treatment condition in which patients were directly exposed to their traumatic memories precludes drawing any firm conclusions about the relative benefits of a phase-based treatment approach over an immediate trauma-focused approach for patients suffering from PTSD related to childhood abuse (see De Jongh et al.) [18]. In other words, the core question is still whether the addition of a stabilization phase is a necessary condition for, and/or has added value over, immediate trauma-focused treatment. And if so, it is important to know which of the two treatment approaches works best for whom. The present study aims to address these questions.

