An improvement in study design relative to previous studies is that the present study specifically focuses on the added value of stabilization. Assessing the two groups after the same amount of treatment sessions (after 8 or 16 sessions) may provide answers to the question as to which of the two conditions works best and in what phase of treatment. Comparing the two conditions post-treatment makes it possible to answer the question whether STAIR has an added value over EMDR only. As some previous studies found that treatment gains emerged only months after treatment has ended [12], the follow-up assessments are pivotal. To ensure that patients engaging in this study represent a group with severe psychopathology, our inclusion and exclusion criteria state that patients must *repeatedly* be exposed to sexual and/or physical abuse during childhood (i.e., complex trauma). Further, psychotic symptoms and bipolar disorders are not excluded with the only exception of those displaying *acute* suicidality at T0. Finally, to increase the generalizability of the results of the present study, we will also include male patients.

There are some potential limitations of the present study that need to be noted. First, instead of exposure therapy as the trauma-focused components, EMDR will be used, rendering a direct comparison more difficult with previous studies that employed PE as the trauma-focused therapy. However, same as PE, EMDR is one of the first-choice trauma-focused treatments for PTSD [1, 2]. An advantage of using EMDR therapy rather than imaginal exposure is that most therapists in the research setting are already well-educated in using EMDR therapy, as EMDR maybe more widely used than other trauma-focused therapies, at least in Europe [63–65].

Furthermore, the quality of assessment of symptoms of complex PTSD is not ideal. While in clinical practice, the term complex PTSD is widely used, definitions of complex PTSD have changed over time and validated diagnostic interviews are not yet available for the current construct of CPTSD as proposed for ICD-11 [11]. Therefore, in this study, the SIDES is used to index severity of complex PTSD and additionally, a variety of psychometrically sound questionnaires to measure the different symptoms associated with complex PTSD separately (e.g. interpersonal functioning, emotion regulation, dissociation).

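### The mixed model as listed has no treatment-by-time term, so its treatment effect averages over all visits and does not estimate the post-treatment and follow-up comparisons the article relies on

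*Protocol article*

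**What the plan says.** The Data analysis section of the protocol article states that "On the continuous outcome measures, the groups will be compared using linear mixed models", and then lists the terms: "Baseline scores will be included as covariates, time as a categorical variable, and treatment condition as a fixed effect". Neither an interaction nor a visit for the primary comparison is named. The hypotheses in the Aim section name no visit either.

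Other sections are more specific about timing:

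- **Study design.** In the phase-based arm "patients will receive eight sessions of stabilization treatment (STAIR), followed by 16 sessions of EMDR therapy"; the other arm has 16 EMDR sessions. Assessments follow every eighth session, post-treatment, and 3 and 6 months later.
- **Discussion.** "Comparing the two conditions post-treatment makes it possible to answer the question whether STAIR has an added value over EMDR only". The same paragraph calls the follow-up assessments pivotal and wants the comparisons after 8 and 16 sessions to show which condition works best in which phase.
- **Power and sample size calculation.** The approximation is a 2 × 5 repeated measures ANOVA "with treatment condition as the between-subjects factor and time as the within-subjects factor", with "alpha 0.05, power 0.80, correlation between measures 0.5, and small effect-size" (f = 0.10), from which "a total sample size of 122 subjects will be required".
- **Background.** On the STAIR phase of the first earlier trial: "There were no improvements in PTSD symptoms, dissociation, and alexithymia".

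**The concern.** With baseline, categorical time and treatment as the only fixed terms, the model assumes the same treatment difference at every post-baseline visit. If the difference changes over time, the coefficient is a weighted average of the visit-specific differences, with equal weights for complete data under compound symmetry.

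In this design a changing difference is to be expected. After eight sessions the arms have had eight STAIR sessions versus eight EMDR sessions. After 16 sessions they have had 8 versus 16 EMDR sessions, and treatment has ended in one arm only. A gap at those visits partly reflects the order of the components and need not persist once both arms have completed EMDR.

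Two things are at stake. The trial's central question, whether STAIR adds value once treatment is complete, would be answered by a quantity that mixes in the period before the STAIR-EMDR arm has had its trauma-focused component. And the listed terms yield no separate estimate at post-treatment, at follow-up or by phase, although the Discussion depends on all three.

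**Working it through.** **1. Which test gives N = 122?** Inputs from the power section: alpha 0.05, rho = 0.5, f = 0.10, two groups, m = 5 time levels.

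- Treatment-by-time interaction: λ = f²·N·m/(1 − rho) = 0.01 × 122 × 5/0.5 = 12.2, with 4 and 480 df. Power is 0.805. At N = 120 it is 0.798, so 122 is the smallest even total. The figure is reproduced. With two groups, the test of time alone gives the same N.
- Between-group main effect: λ = f²·N·m/(1 + (m − 1)·rho) = 6.1/3 = 2.03, with 1 and 120 df. Power is 0.29, and 80% power needs N = 474. The figure is not reproduced.

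This shows which test the sample size belongs to. The 0.29 is not the power of the listed model, because the ANOVA main effect includes the baseline visit and is not baseline-adjusted. For two equal groups f = 0.10 corresponds to d = 2f = 0.2. A constant 0.2 SD difference in the baseline-adjusted four-visit average gives 0.2/0.111 = 1.80 standard errors (SE from step 2), about 43% power. On either calculation, 122 was not derived for this coefficient.

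**2. Precision of the possible contrasts.** Assumptions: 122 complete cases, 1:1 allocation (the article states no ratio), unit SD, compound symmetry with rho = 0.5, baseline as covariate, and four post-baseline visits (the five ANOVA levels less baseline). For the mean of q visits:

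Variance = (1 + (q − 1)·0.5)/q − 0.25; SE = √(4/122 × variance)

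| Contrast | q | Variance | SE (SD units) |
|---|---|---|---|
| Single visit | 1 | 0.750 | 0.157 |
| Mean of post-treatment, 3 and 6 months | 3 | 0.417 | 0.117 |
| All four visits | 4 | 0.375 | 0.111 |

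**3. True later benefit.** Assume STAIR-EMDR is 0.4 SD better at post-treatment, 3 and 6 months, and x SD worse after eight sessions. The all-visit effect is (3 × 0.4 − x)/4. Power is from the noncentral t.

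| x (SD) | All-visit effect (SD) | Power, all-visit |
|---|---|---|
| 0 | 0.300 | 77% |
| 0.2 | 0.250 | 61% |
| 0.5 | 0.175 | 35% |
| 0.8 | 0.100 | 15% |
| 1.0 | 0.050 | 7% |

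The other two contrasts do not depend on x: 0.4/0.157 gives 72% for a single visit, and 0.4/0.117 gives 92% for the three-visit mean.

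**4. Arms equal at the end.** If the arms are identical at the three later visits, the all-visit effect is −x/4. For x = 0.5 it is −0.125 SD and for x = 1.0 it is −0.25 SD. The two-sided test is then significant in 20% and 61% of trials.

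**5. Visit structure.** The article does not place the 16-session assessment in the five ANOVA levels. For STAIR-EMDR it is mid-treatment, with post-treatment after session 24; for EMDR alone, session 16 ends treatment. The levels of categorical time therefore do not align between arms, and the four-visit layout above is a simplification.

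**The case against.** The strongest reply is that a condensed article is being read too literally. The sentence covers all continuous outcomes, does not call the listed terms exhaustive, and does not exclude an interaction. The power section and the Discussion suggest that time-specific comparisons were intended, and the full protocol or SAP may contain them. This stands in part: a reader might infer that the authors decided on a main-effect-only model, and the article does not support that. But it does list the model's terms one by one, and an analyst who followed the list would not obtain the comparisons described elsewhere.

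A reader might also infer that the model biases the primary answer against STAIR-EMDR. That goes too far. A time-averaged effect is a legitimate estimand if chosen, and the article names no primary visit against which bias could be measured. Earlier relief is even part of the debate, since the Discussion cites the argument that stabilization delays access to effective treatment. The distortion exists only relative to the post-treatment and follow-up question.

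Nor is it established that STAIR-EMDR will lag after eight sessions. The Background sentence concerns one phase of one trial. The second trial described there found no significant differences in loss of diagnosis immediately after treatment, although one of its arms combined STAIR with supportive counselling and had no exposure. A lag is plausible, but its size is unknown. With no lag, the all-visit coefficient (77%) has more power than a single-visit contrast (72%).

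**Conclusion.** The concern holds for the model as listed. Its treatment coefficient is an all-visit average that includes the eight-session assessment, before any EMDR in the STAIR-EMDR arm. It does not estimate the comparisons the Discussion says answer the question, and it is not the test that reproduces N = 122.

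These points follow from the text. The direction of the pull is conditional: the average moves against STAIR-EMDR, relative to the post-treatment contrast, only if EMDR reduces PTSD symptoms more than STAIR does in the first eight sessions. The size rests on assumptions, because the article gives no SD or effect by visit. For a later benefit of 0.4 SD and early deficits of 0 to 1.0 SD, all-visit power runs from 77% to 7%, against 72% and 92% for the two alternatives. The 20% to 61% rejection rates when the arms end equal need early deficits of 0.5 to 1.0 SD, and should not be read as a forecast.

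**What to change.** State the model as baseline PSS-SR, categorical time, treatment and treatment-by-time, with a flexible residual covariance. Test hypothesis 1 on the PSS-SR with one prespecified contrast that leaves out the during-treatment visits. Two choices fit the article: the baseline-adjusted difference at post-treatment, which is the comparison the Discussion names, or the mean difference over post-treatment, 3 and 6 months. The article does not single out the 6-month visit, so using it alone would need its own justification.

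Report the 8-session, 16-session and individual follow-up contrasts from the same model as secondary. Define the time levels so that session 16, which ends treatment in one arm only, is not treated as post-treatment in the other.

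The change is to wording, made before outcome data are analysed, and needs no new data. A single-visit contrast is less precise than the all-visit average (SE 0.157 versus 0.111 SD); the three-visit mean loses little (0.117). Since 122 was derived for an omnibus interaction, state what it can detect for the chosen contrast. Under the assumptions above, 80% power needs about 2.80 × 0.157 = 0.44 SD at one visit, or 2.80 × 0.117 = 0.33 SD for the three-visit mean, before dropout.
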